### Interventions

#### ProYouth

Participants randomized to the control condition will participate in ProYouth [41] for 6 weeks. ProYouth is an Internet-based intervention for the prevention and early intervention of EDs. It consists of modules with different intensities, and participants can utilize the program in accordance with their individual needs and preferences. ProYouth includes a comprehensive section on psychoeducation, a forum for peer-to-peer support, and optional online chats with a psychologist. In addition, ProYouth includes a monitoring and feedback system; i.e., once a week participants receive an email invitation to answer a short online questionnaire on their Smartphone or PC and directly receive personalized feedback on their current status and the development of ED-related attitudes, behaviors, and symptoms over time. In case participants develop severe ED symptomatology during their participation, a ProYouth counselor automatically receives a notification via email. The counselor then contacts the participant personally and invites her/him to an individual chat session in order to clarify the need for further support. If needed, the counselor offers the participant assistance in seeking professional face-to-face help.

#### ProYouth-DISS

A structured dissonance-based intervention will be provided as an add-on to ProYouth; i.e., participants will have access to an enhanced version of ProYouth for 6 weeks. The ProYouth-DISS intervention aims at reducing ED risk factors by inducing cognitive dissonance. This approach assumes that the thin ideal and thin-ideal internalization play a major role in the development of ED. Internalized thin ideals in combination with social comparison processes result in increased body dissatisfaction. High levels of body dissatisfaction can cause dieting, restrained eating, and other compensatory measures to reduce body weight. This can be considered one of the developmental pathways of ED. ProYouth-DISS aims at counteracting these processes by influencing the internalized thin ideal and other weight- and shape-related beliefs and attitudes. As part of the intervention, participants will be asked to actively criticize such dysfunctional attitudes and beliefs. The discrepancy between the participants’ own beliefs and attitudes and the position they are representing in this situation causes dissonance. Because of the human tendency to seek consistency between attitudes and behaviors, this dissonance is reduced by a change of beliefs and attitudes (e.g., thin-ideal internalization, body dissatisfaction). Female participants will learn to challenge the thin ideal. In addition, they will be asked to engage in exercises aimed at reducing body image concerns. Male participants have access to an adapted version of ProYouth-DISS that challenges the muscular body ideal [42]. Videos with peers guide participants through the program and motivate them to attend the sessions. Participants work through the materials individually and may interact with a counselor on demand. The module consists of six sessions. As part of the weekly ProYouth monitoring emails, participants will be reminded to complete the ProYouth-DISS sessions. In addition to the structured ProYouth-DISS module, participants are encouraged to use the standard ProYouth modules.

#### ProYouth-GROUP

A clinician-guided CBT group intervention will be provided as an add-on to ProYouth. The preliminary efficacy of CBT interventions in terms of reduction of body image problems and ED symptoms has been confirmed in both face-to-face and online settings [27]. Based on this evidence, the ProYouth-GROUP intervention will use a CBT approach to address factors that contribute to the development and maintenance of body dissatisfaction, weight/shape concerns, and disordered eating. A specific focus will be on environmental risk factors such as stigmatization and the perceived pressure from peers and media to conform to social appearance ideals. This pressure is assumed to increase both the internalization of social appearance ideals and body comparison tendencies, which subsequently lead to an increase of body dissatisfaction, weight/shape concerns, and disordered eating. Therefore, the ProYouth-GROUP intervention will teach skills for understanding and counteracting such pressures from peers and media and convey ways how to normalize one’s own eating behavior. The group chats focus on topics such as media influences on body dissatisfaction, strategies to improve self-esteem and body image, and emotion regulation skills. In addition, participants are asked to engage in cognitive behavioral exercises following each session. The last session will highlight the importance of seeking help early, discuss barriers to help-seeking, and illustrate strategies on where and how to seek professional help. The intervention consists of six 90-min group chat sessions facilitated by a qualified psychologist. Separate groups will be established for female and male participants. Videos with peers guide participants through the program and motivate them to attend the chat sessions. They are also reminded to join the chat sessions as part of the weekly ProYouth monitoring emails. In addition to this structured module, participants are encouraged to use the standard ProYouth modules.

### Assessments, measures, and outcomes

Three assessments are conducted at participants’ high schools (i.e., screening, 12 months follow-up, and 24 months follow-up) as part of the CP of the ProHEAD Consortium. Additional trial-specific assessments are conducted prior to randomization (baseline), at the end of the intervention (after 6 weeks), and at 6 months follow-up (Fig. 2). All assessments are based on self-report and conducted online via the ProHEAD platform.

### Screening

ED-related eligibility criteria will be checked via two screening instruments. The Weight Concerns Scale (WCS) is a one-dimensional instrument consisting of five Likert items that assesses concerns about body weight. A WCS score > 57 is associated with an elevated risk for developing an ED [33, 34]. The Short Evaluation of Eating Disorders (SEED; [35]) assesses body weight and height used to calculate the BMI as well as key ED symptoms (fear of weight gain, distortion of body perception, over-concern with weight and shape, frequency of binge eating, frequency of compensatory behaviors) over the past 4 weeks.

### Primary outcome

The primary outcome of the present trial is ED symptomatology at the end of the intervention assessed with the child version of the Eating Disorder Examination-Questionnaire (ChEDE-Q; [43]). The ChEDE-Q measures disordered eating over a 28-day period and includes 28 items and four subscales (Eating Concern, Shape Concern, Weight Concern, and Dietary Restraint) as well as a global score, which is an average of the subscales.

### Secondary outcomes

Secondary outcomes include ED symptomatology at 6, 12, and 24 months follow-up measured with the ChEDE-Q and the SEED. Additional outcomes are body dissatisfaction, appearance ideal internalization, ED-related stigma, and ED-related help-seeking at the end of the intervention and at 6 months follow-up. Body dissatisfaction is measured with the 8-item version of the widely used Body Shape Questionnaire (BSQ; [44, 45]). Research on the brief version (BSQ-8C) demonstrated good psychometric properties and sensitivity to change [46]. Items are rated on a 6-point Likert scale from 1 = “never” to 6 = “always”, with higher scores indicating higher levels of body dissatisfaction. Appearance ideal internalization is assessed using the internalization subscale of the German version of the Sociocultural Attitudes Towards Appearance Questionnaire (SATAQ-G) for female and male participants, respectively [47]. It consists of 6 items reflecting the adoption of the thin or muscular ideal as a personal standard. Stigma is measured with the ED-specific version of the Universal Stigma Scale (USS; [48]). The USS is an 11-item instrument. It consists of two subscales (impairment/distrust, blame/personal responsibility), with internal consistencies between 0.72 and 0.83 across different samples [48]. ED-related help-seeking is measured with an ED-specific version of the General Help-Seeking Questionnaire (GHSQ; [49]), a frequently used measure for help-seeking for psychological complaints. Acceptance of the online interventions (ProYouth, ProYouth-DISS, ProYouth GROUP) will be assessed with the German version of the Client Satisfaction Questionnaire (ZUF-8; [50]) adapted for the online setting. The ZUF-8 measures participants’ satisfaction with the intervention. Finally, compliance with the interventions and utilization of the various modules will be analyzed based on automatically recorded server logs.

### Health economic evaluation

The health economic evaluation will include an analysis of the cost-effectiveness and cost-utility of the interventions. In addition to the costs of the interventions, health-related quality of life and healthcare utilization will be assessed at 12 months follow-up using the KIDSCREEN-10 [51] and the Mannheimer Modul Ressourcenverbrauch (MRV; [52]), respectively. The KIDSCREEN-10 is a widely used 10-item instrument for the assessment of health-related quality of life. The MRV assesses detailed information on utilization of treatment for any kind of health problem (inpatient care, outpatient care, medication) within the past 12 months.

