### Recruitment and study procedures

The ProHEAD Consortium will recruit a school-based sample of 15,000 C&A aged 12 or older in grades 6–13 in five regions of Germany (Hamburg, Heidelberg, Leipzig, Marburg, Schwäbisch Gmünd). The procedures with respect to selection of schools are described in the study protocol of sub-project 1 of the ProHEAD Consortium [29].

Written informed consent will be obtained from C&A and their legal guardians prior to inclusion into the project. As part of the ProHEAD CP, assessments of sociodemographic information, healthcare utilization, help-seeking, and a broad variety of mental health problems and health-risk behaviors will be included in the screening and the two annual follow-ups. These three annual assessments will be conducted electronically via the ProHEAD online platform in the computer rooms of the respective schools (for details on the instruments used at the school-based assessments, see the study protocols of the other ProHEAD sub-projects in this issue [29–32]). Based on the screening results, each participant will be allocated to one of the five ProHEAD RCTs. Participants who meet eligibility criteria for more than one RCT will be randomly allocated to one of the sub-projects.

Participants assigned to the present ED trial will receive an email inviting them to register for the study. In order to enroll, they will need to click on a link in this email to activate their user account and to complete a trial-specific baseline online assessment. Upon completion of this assessment, they will be randomized to one of the three study arms and then have access to the respective intervention (ProYouth, ProYouth-DISS, or ProYouth-GROUP) for a duration of 6 weeks. Trial-specific post and follow-up assessments will be conducted online 6 weeks after randomization and 6 months later (Fig. 1).

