### Statistical analysis

Primary data analyses will be based on the intention-to-treat (ITT) population; i.e., all participants randomized to one of the three study conditions will be included in the primary outcome analysis. Missing data patterns will be explored. Multiple imputations will be applied to impute missing data.

Repeated measures ANOVA will be conducted (time*group interaction, alpha = 5%) to test the primary hypothesis, i.e., differences in efficacy between the interventions. For the primary outcome, only the baseline and the post assessment after 6 weeks will be considered. In case of statistically significant differences, post hoc pairwise group comparisons will be conducted (Bonferroni correction). Repeated measures ANOVA will also be conducted to determine the effect of the interventions on metric secondary outcomes. Post-intervention symptom courses will be analyzed applying mixed effects models. In order to investigate gender-specific efficacy, multifactor ANOVAs will be conducted. Fisher’s exact test will be applied to compare actual help-seeking between the groups.

For the health economic evaluation, data on the costs of interventions and efficacy will be used to determine the incremental cost-effectiveness ratio (ICER) of the interventions. The ICER will provide the additional costs in monetary terms of the respective programs to be spent for gaining an additional outcome unit. Cost-utility analyses will provide information on cost per quality-adjusted life years (QALYs) gained by the various interventions. Bootstrapping procedures will be applied to provide cost-effectiveness planes and acceptability curves.

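### Cost per QALY gained is promised, but quality of life is stated at 12 months and at none of the trial-specific assessments, so gains that fade within the year would be missed or understated

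*Protocol article*

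**What the plan says.** Under Health economic evaluation, the article places both economic measures at one wave: "health-related quality of life and healthcare utilization will be assessed at 12 months follow-up using the KIDSCREEN-10" and, for resource use, the MRV, which asks about the preceding 12 months. Under Statistical analysis it then commits to a QALY output: "Cost-utility analyses will provide information on cost per quality-adjusted life years (QALYs) gained by the various interventions".

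Two sets of assessments exist (Assessments, measures, and outcomes). The school-based waves are "screening, 12 months follow-up, and 24 months follow-up". The trial's own online waves are described thus: "Additional trial-specific assessments are conducted prior to randomization (baseline), at the end of the intervention (after 6 weeks), and at 6 months follow-up". Quality of life is not assigned to any of the online waves, and Secondary outcomes, which dates its symptom, body-image, stigma and help-seeking measures, contains no quality-of-life measure.

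On the content of the school waves, Recruitment and study procedures gives a general list ("assessments of sociodemographic information, healthcare utilization, help-seeking, and a broad variety of mental health problems and health-risk behaviors will be included in the screening", and in both annual follow-ups). It then refers elsewhere for the instruments: "for details on the instruments used at the school-based assessments, see the study protocols of the other ProHEAD sub-projects in this issue". Participants have access to their intervention "for a duration of 6 weeks".

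**The concern.** A QALY difference is the area between the arms' utility curves from randomization to the horizon. One value at month 12 fixes the end of that curve and nothing before it. The intervention lasts six weeks and the primary outcome is taken at its end, so an early effect is at least plausible, and that is the stretch with no stated utility measurement. The cost side does cover the year, because the MRV looks back over 12 months. A year of costs would then be set against a health state observed at its end.

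If the arms have converged by month 12, the incremental QALY estimate is close to zero whatever happened earlier, and the cost per QALY, the bootstrapped plane and the acceptability curve all inherit that. The article presents the economic evaluation as one of the trial's objectives and as an input to reimbursement decisions, so the QALY result is likely to be read at face value.

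**Working it through.** The article gives no QALY figure, so there is none to reproduce. The check asks what a 12-month value can recover under assumed utility profiles.

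**Inputs from the article:** quality of life at 12 months; online assessments at baseline, 6 weeks and 6 months; 103 participants per arm; 20% dropout.

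**Assumed, not in the article:** between-arm utility difference peaking at 0.02 to 0.10; utility SD 0.10 to 0.20; equal utilities at randomization; month 6 and month 12 counted from randomization.

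**Step 1. Formula.** QALY difference = sum over intervals of (interval length in years) × (mean of the two end differences). Week 6 is 6/52 = 0.1154 year.

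**Step 2. Gain of 0.04 by week 6, held to month 6, gone at month 12.**
- 0 to week 6: 0.1154 × 0.04/2 = 0.0023
- week 6 to month 6: 0.3846 × 0.04 = 0.0154
- month 6 to month 12: 0.5 × 0.04/2 = 0.0100
- total: 0.0277 QALY

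If the 6-month assessment is counted from week 6, the total is 0.0023 + 0.0200 + 0.3846 × 0.04/2 = 0.0300.

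**Step 3. Range of profiles, peak at week 6.**

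| Peak gain | Gone by month 6 (0.25 × peak) | Gone by month 12 (0.5 × peak) | From the 12-month value alone |
|---|---|---|---|
| 0.02 | 0.005 | 0.010 | 0 |
| 0.05 | 0.0125 | 0.025 | 0 |
| 0.10 | 0.025 | 0.050 | 0 |

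The last column assumes equal baselines and a straight line, which gives 0.5 × the 12-month difference.

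**Step 4. Gain that does not fade.** A gain of 0.05 reached at week 6 and sustained is worth 0.1154 × 0.05/2 + 0.8846 × 0.05 = 0.0471. The straight line from the 12-month value gives 0.5 × 0.05 = 0.025. So even a lasting effect is roughly halved under that interpolation.

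**Step 5. Which added measurements help.** Adding a pre-randomization value alone permits change scores and adjustment but still returns 0 for every profile in Step 3. Only values at week 6 and month 6 recover them.

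**Step 6. If no pre-randomization value exists.** The SE of a chance baseline difference between two arms is SD × √(2/n). With n = 103, √(2/103) = 0.139 SD, or 0.014 to 0.028 in utility. With 103 × 0.8 ≈ 82, it is 0.156 SD, or 0.016 to 0.031. Adjustment for a baseline value that correlates 0.3, 0.5 or 0.7 with the 12-month value would reduce the variance to 1 − r² = 91%, 75% or 51%.

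**The case against.** The strongest reply is that the sentence on the KIDSCREEN-10 names 12 months but does not say that it is the sole time point. The same sentence gives 12 months for healthcare utilization, although Recruitment and study procedures also puts utilization at screening and at 24 months. The sentence is therefore not a full schedule. The general list of school-wave content omits quality of life, but it covers all three waves, including the 12-month wave where the KIDSCREEN-10 is expressly placed. Its silence therefore proves nothing about screening. Fig. 2 is not available here, and its legend also omits other school-wave instruments such as the PHQ-A, AUDIT, SDQ and MRV. Instrument details are deferred to companion protocols that are not shown.

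This stands. A reader might infer that no starting value exists and that baseline adjustment is ruled out; the article does not establish that, since a screening value would precede randomization and supply both. Nor is the absence of a stated conversion from KIDSCREEN-10 to utilities an error, because a condensed article may leave that step to the fuller plan.

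Two further points stand. Chance imbalance between randomized arms is imprecision, which the planned bootstrap reflects, not bias. And nothing in the article shows that the effect must peak early; averted onset could pay off later.

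The reply does not reach the gap between randomization and month 12. The school waves fall at screening, 12 and 24 months, so a screening KIDSCREEN-10 would leave week 6 and month 6 unmeasured, and no online assessment is said to fill them.

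**Conclusion.** The point holds in a limited form. The article commits to cost per QALY gained while stating no quality-of-life measurement between randomization and month 12. A benefit that comes and goes within the year is missed if the arms have fully converged by then, and understated if they have partly converged. On the assumed profiles in the table, the loss is 0.005 to 0.050 QALY; these are illustrations, not estimates for this trial.

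The baseline part is conditional: QALYs could not be baseline-adjusted unless the school screening includes the KIDSCREEN-10, which the article leaves open.

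It would go too far to conclude that the cost-utility plane and acceptability curve are bound to be wrong. A 12-month comparison between randomized arms remains valid for that time point; it is the step from there to QALYs over the year that lacks data. The primary outcome is untouched, and so is the cost-effectiveness ratio, which uses the efficacy data. This is a cheap improvement to a secondary analysis.

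**What to change.** - Add the ten-item KIDSCREEN-10 to the existing online 6-week and 6-month assessments, and to the online baseline if it is not already in the school screening. If it is in the screening, say so in one sentence.
- Define QALYs as the baseline-adjusted area under the utility curve from randomization to month 12.
- For participants already enrolled (Trial status reports that recruitment has begun), use the screening value as baseline if one exists.
- If these measurements cannot be obtained, report the cost-utility result as a 12-month comparison that does not capture earlier gains, and rely on cost per ChEDE-Q unit for the economic conclusion.

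Cost: an amendment, ten extra items at two or three online assessments, and early values that remain missing for those who have already passed them.

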### Sample size calculation

We assume a small to medium effect (superiority of the two intervention groups over the control condition) on ED symptomatology. Repeated measures analysis of variance (ANOVA) will be conducted (time*group interaction, alpha = 5%). Assuming an effect of *f* = 0.15, a dropout rate of 20%, and correlations of 0.1 among repeated measures, 309 subjects need to be recruited (103 per group) to test the global hypothesis with 90% power. In case of significant findings for the main effect of study group, the proposed sample size will allow for post hoc pairwise group comparisons at a power above 80%.

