### Randomization and blinding

Eligible C&A will be randomized to one of the three interventions based on an allocation sequence derived from a computerized random number generator at a 1:1:1 ratio. The allocation scheme is embedded into the ProHEAD online platform; i.e., participants are automatically assigned to one of the study arms and informed electronically about the outcome without researchers having access to the allocation scheme. Randomization will be stratified by gender. Due to the study characteristics, blinding of participants and/or online counselors is not possible because participants will be informed as to which intervention they were assigned, and counselors need to provide guidance accordingly.

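### The effect called small to medium (f = 0.15 on a two-occasion interaction) is a difference from control of about 0.64 SD of a ChEDE-Q score; the metric should be stated

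*Protocol article*

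**What the plan says.** The Sample size calculation section of the Protocol article opens: "We assume a small to medium effect (superiority of the two intervention groups over the control condition) on ED symptomatology". The planned test is the time-by-group interaction of a repeated measures ANOVA at alpha 5%. The inputs are: "Assuming an effect of *f* = 0.15", with "a dropout rate of 20%, and correlations of 0.1 among repeated measures". The result is that "309 subjects need to be recruited (103 per group) to test the global hypothesis with 90% power".

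The Statistical analysis section fixes the number of occasions: "For the primary outcome, only the baseline and the post assessment after 6 weeks will be considered". Randomization and blinding gives three arms of equal size.

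The article does not translate f into a ChEDE-Q difference or a standardised mean difference. It gives no source for f or for the correlation.

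**The concern.** Cohen's f has familiar benchmarks (0.10 small, 0.25 medium) for the spread of group means in a one-way comparison. A reader who sees f = 0.15 beside the small-to-medium label will take it as a modest difference between arms. In a two-occasion interaction, however, each interaction effect is half of an arm's deviation in change. The same f therefore describes a post-intervention contrast twice as large as the one-way reading suggests.

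What is at stake is the meaning of the 90% power. The comparator is an active program, so the size of difference the trial can detect matters for interpretation. The article gives no figure from which a reader could see it.

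**Working it through.** **Inputs.** From the article: k = 3 arms, m = 2 occasions, f = 0.15, correlation rho = 0.1, alpha = 0.05, 20% dropout, 309 recruited.

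**1. Reproducing 309.** For the interaction, lambda = f² × N × m / (1 − rho), with 2 and N − 3 degrees of freedom.
- Here lambda = 0.0225 × N × 2 / 0.9 = 0.05N. Power reaches 90% at N = 257 completers.
- 257 × 1.2 = 308.4, rounded up to 309, the stated figure. (257 / 0.8 would give 322.)
- 309 × 0.8 ≈ 247 completers, lambda = 12.35, power 88.9%. The form of the dropout inflation therefore costs only about one point.
- Other readings of f do not give 309. A main effect of group needs 313 completers, and lambda = f² × N needs 566.

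**2. Converting f to a difference between arms.** Assume equal baselines and both interventions shifted by d at 6 weeks, in SDs of one measurement.
- The SD of (0, d, d) is d × √(2/9) = 0.471d.
- The interaction effects are half of this: f = 0.236d.
- d = 0.15 / 0.2357 = 0.636 SD.
- Evenly spaced arms (0, d/2, d) would give 0.735 SD between the extreme arms.
- Check: N × (2/9) × 0.636² / 1.8 = 0.05N, the lambda in step 1.

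**3. The same effect on other scales.**
- Change score: its SD is √(2 × 0.9) = 1.342, so 0.636 / 1.342 = 0.47 SD. The one-way f on change is √0.05 = 0.22.
- Post-intervention means: f = 0.471 × 0.636 = 0.30.
- Had f = 0.15 been meant on post-intervention means, d would be 0.15 / 0.471 = 0.32 SD.

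**4. Power of the planned test** (247 completers, rho = 0.1), with lambda = 247 × (2/9) × d² / 1.8:

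| d (score SD) | lambda | Power |
|---|---|---|
| 0.20 | 1.22 | 15% |
| 0.35 | 3.74 | 39% |
| 0.40 | 4.88 | 49% |
| 0.50 | 7.62 | 69% |
| 0.636 | 12.35 | 89% |

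At 0.32 SD power is 33%, and it reaches 50% at about 0.41 SD. Simulation of the change-score ANOVA with 82 per arm gave 15.5%, 38.9%, 68.5% and 88.4% at 0.20, 0.35, 0.50 and 0.636 SD.

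**5. Difference detectable with 90% power, 247 completers.** For the ANCOVA, lambda = N × (2/9) × d² / (1 − rho²). Only rho = 0.1 is in the plan; 0.5 and 0.7 are assumptions that show the range.

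| rho | Planned interaction test | ANCOVA adjusted for baseline |
|---|---|---|
| 0.1 | 0.65 SD | 0.48 SD |
| 0.5 | 0.48 SD | 0.42 SD |
| 0.7 | 0.37 SD | 0.35 SD |

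**The case against.** **Nothing is miscalculated.** The inputs are stated, and the N and (within about a point) the power reproduce. A reader might infer that the sample size is wrong; the article does not support that. This stands in full.

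**The label fits the scale used.** An f of 0.15 lies between the usual small and medium values. On the change score, which is what a two-occasion interaction tests, the effect is 0.47 SD with a one-way f of 0.22, both just under the usual medium values. This also stands. The label fails only when read as a between-arm difference in score SDs, and the article does not say which reading is meant.

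**Power is not below one half for every small-to-medium effect.** A reader might infer that it is. On the benchmarks of 0.2 and 0.5 SD, which are an assumption because the article defines no such range, power runs from 15% to 69%. It is clearly below one half at 0.32 and 0.35 SD, about one half at 0.40 and above it beyond 0.41. What holds across the range is that power falls short of 90%, by about 20 points even at 0.50 SD.

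**The shortfall depends on "correlations of 0.1 among repeated measures".** If the true correlation were higher, the planned test would do better: at 0.35 SD, 63% with rho = 0.5 and 86% with rho = 0.7. This stands, but 0.1 is the plan's own input and its claim has to be read on it.

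**The Background does not settle the target.** One might argue from its remark on mostly small effects that a smaller target was needed. That remark summarises one review of mixed programs, gives no numerical effect, and stands beside the finding that selective, interactive and multi-session programs did better. Nor does a planning label decide what a null result excludes; the confidence interval would.

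**A full protocol may hold the translation.** Possibly. But this article itself attaches a size label to an f whose metric it does not name.

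**Conclusion.** The point holds as one of unclear and potentially misleading specification, not of arithmetic. Under the plan's inputs, 90% power (88.9% with 247 completers) refers to a difference of about 0.64 SD of a ChEDE-Q score between each intervention and control. The small-to-medium label can be defended on the interaction or change-score scale, but not as a between-arm difference in score SDs.

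The 0.64 SD rests on the article's own f and two occasions, the named pattern of both interventions better than control, and equal baselines. The 0.47 SD of change and the power figures also rest on rho = 0.1, and the power figures on 247 completers as well. Judging any of these values as small or medium uses benchmarks from outside the document.

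**What to change.** Keep N at 309. In the Sample size calculation section, say that f is defined on the two-occasion interaction. In place of the unqualified small-to-medium label, give the target as about 0.64 SD of the ChEDE-Q global score versus control under the current inputs. This costs one or two sentences, and a target that reads less favourably.

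Preferably, also make the primary test an ANCOVA of the 6-week score adjusted for baseline, and quote its detectable difference over a range of correlations: 0.48 SD at 0.1, 0.42 at 0.5 and 0.35 at 0.7 with 247 completers and 90% power. The baseline is already collected before randomization, so no further data or participants are needed. The cost is an amendment of the primary analysis, to be made before outcome data are examined.

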**Methods:**

The trial is one of five sub-projects of the German multicenter consortium ProHEAD. It is a three-arm, parallel, randomized controlled superiority trial. Participants will be randomized to (1) the online program ProYouth (active control condition) or (2) ProYouth plus a structured dissonance-based module or (3) ProYouth plus a CBT-based chat group intervention. As part of ProHEAD, a representative school-based sample of *N* = 15,000 students (≥ 12 years) will be screened for mental health problems. *N* = 309 participants at risk for ED (assessed with the Weight Concerns Scale (WCS) and the Short Evaluation of Eating Disorders (SEED)) will be included in the present trial. Online assessments will be conducted at baseline, at end of intervention (6 weeks), at 6 months follow-up, and — as part of ProHEAD — at 12 and 24 months follow-up. The primary outcome is ED-related impairment (assessed with the Child version of the Eating Disorder Examination-Questionnaire (ChEDE-Q)) at the end of the intervention. Secondary outcomes include ED-related symptomatology at follow-up, ED-related stigma, ED-related help-seeking, and acceptance of and compliance with the interventions. For the health economic evaluation data on costs of the interventions, healthcare utilization and health-related quality of life will be assessed.

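### At the stated inputs, 309 recruited with 20% counted as lost gives about 89% power, not 90%; the figure is consistent with a ×1.2 dropout allowance

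*Protocol article*

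**What the plan says.** The Sample size calculation section of the protocol article bases the trial on a repeated measures ANOVA that "will be conducted (time*group interaction, alpha = 5"%). It assumes a small to medium effect, f = 0.15, and then "a dropout rate of 20%, and correlations of 0.1 among repeated measures, 309 subjects need to be recruited (103 per group"), which is said to be enough "to test the global hypothesis with 90% power".

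The Statistical analysis section names the same test for the primary hypothesis: "Repeated measures ANOVA will be conducted (time*group interaction, alpha = 5%) to test the primary hypothesis". It limits the data used: "For the primary outcome, only the baseline and the post assessment after 6 weeks will be considered". It also says that every randomised participant enters the primary analysis, with multiple imputation of missing values. The Randomization and blinding section gives three arms at 1:1:1.

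The article does not print the number of completers required or the formula that turns it into a recruitment target.

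**The concern.** The section states every input needed to recompute the sample size, together with the result, so the figures can be checked against each other. A dropout rate of 20% means that 80% of those recruited remain, so the evaluable number should be divided by 0.8. Adding 20% to the evaluable number is a common slip that leaves too few after the loss: 1.2 × 0.8 = 0.96, so 4% of the required completers are missing.

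At stake is whether the recruitment target, the dropout allowance and the power claim agree. Readers will judge the trial's result against that power claim. The dropout allowance is also the input that the authors themselves treat as uncertain: the Discussion warns that study dropout may be high in online trials of this kind.

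**Working it through.** **Inputs**

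- Test: time-by-group interaction, alpha 0.05 (Sample size calculation; Statistical analysis).
- Effect f = 0.15, correlation ρ = 0.1, dropout 20%, power 90%, recruit 309 (Sample size calculation).
- Occasions m = 2, baseline and 6 weeks (Statistical analysis).
- Groups k = 3, allocated 1:1:1 (Randomization and blinding).

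**Step 1. Evaluable number required**

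The noncentral F calculation for a within-between interaction uses

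λ = f² · N · m / (1 − ρ), with df1 = (k − 1)(m − 1) and df2 = (N − k)(m − 1).

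Here λ = 0.0225 × 2 × N / 0.9 = 0.05 N, with df 2 and N − 3.

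| Evaluable N | λ | Power |
|---|---|---|
| 247 | 12.35 | 0.8885 |
| 256 | 12.80 | 0.8999 |
| 257 | 12.85 | 0.9011 |
| 258 | 12.90 | 0.9023 |
| 309 | 15.45 | 0.9481 |

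The smallest N reaching 90% is 257, or 258 with equal arms.

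**Step 2. Reproducing 309**

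- Adding 20%: 257 × 1.2 = 308.4, rounded up to 309 = 3 × 103. This is the printed figure.
- Allowing for a 20% loss: 257 / 0.8 = 321.25, rounded up to 322, or 324 = 3 × 108 for equal arms.

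Other readings at 90% power, with division by 0.8, do not give 309. Three occasions give 260 for the interaction. A between-groups effect gives 392 with two occasions and 285 with three. Defining f directly on the change score needs 566 evaluable before any dropout allowance.

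**Step 3. Power at the stated recruitment and dropout**

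309 × 0.8 = 247.2, so about 247 remain and power is 88.9%. The gap is 90 − 88.9 = 1.1 percentage points. In participants it is 322 − 309 = 13, or 324 − 309 = 15 with equal arms. The largest dropout that still leaves 257 is 1 − 257/309 = 16.8%. This step uses only the stated inputs and does not depend on how 309 was reached.

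**Step 4. What multiple imputation could recover**

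All randomised participants have a baseline, because it is completed before randomisation (Recruitment and study procedures). Suppose that 20% lack the 6-week value, that data are missing at random (an assumption), and that the imputation uses all 309 baselines. With unit variances, the variance of the mean change is proportional to

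(1 − ρ²)/247.2 + (1 − ρ)²/309 = 0.99/247.2 + 0.81/309 = 0.004005 + 0.002621 = 0.006626.

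Setting this equal to 2(1 − ρ)/N_eff = 1.8/N_eff gives N_eff ≈ 272 and power of about 91.7%. A simulation of the limiting case with many imputations also gave 91.7%; one with 20 imputations gave 90.3%. A fair range is 90 to 92%.

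**The case against.** The strongest reply is that counting dropouts as wholly lost is not the analysis planned. The primary analysis keeps all randomised participants and imputes missing values, and under missing at random Step 4 puts power at 90% or slightly above. This stands as a statement about the eventual analysis, and it rules out a flat claim that the trial misses 90%. It does not reconcile the printed calculation. The sample size section treats dropout as a loss to be made up by recruitment and does not mention imputation, and the missing-at-random condition is not stated there.

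A second reply is that the gap is trivial beside the uncertainty in the inputs. With 247 evaluable, a correlation of 0.13 instead of 0.1 gives 89.9%, and f = 0.153 instead of 0.15 gives 90.1%. That is correct, and it limits the weight of the point. It does not make the stated figures agree.

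A third reply is that the ×1.2 step is nowhere in the text. That is also correct. A reader might take the exact match as proof of how 309 was obtained, but the article shows neither 257 nor the factor. All that can be said is that 309 is consistent with that step and that none of the other readings tried reproduces it.

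**Conclusion.** The point holds as a minor arithmetic inconsistency. At the stated effect, correlation, alpha and design, 309 recruited with 20% counted as lost gives 88.9% power. The stated 90% is supported only up to about 17% dropout. The calculation rests on the usual within-between definition of f, which is the convention under which the printed inputs lead to 309.

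A reader might go further and infer that the trial is underpowered or must enrol more. The documents do not support that. The shortfall is 1.1 points, or 13 to 15 participants, and the planned intention-to-treat analysis with multiple imputation could remove it if data are missing at random. The figures of 322 and 324 show the size of the discrepancy; they are not a recommended target.

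**What to change.** Keep 309 and correct one sentence in the Sample size calculation section, in one of two ways:

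- State that 309 recruited gives about 89% power for the global test when 20% are counted as lost, or equivalently 90% with dropout up to about 17%.
- State that the 90% relies on analysing all randomised participants with multiple imputation under missing at random, and give the calculation behind it.

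Either way, print the required evaluable number (257, or 258 for equal arms) so that the dropout step can be followed. The cost is one sentence and, under the first option, a slightly less favourable power figure. Enrolment, conduct and the analysis do not change, and every other mention of 309 can stay.
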